### 10.1. Primary study parameter(s)

The main comparison of the primary outcome parameters will be between the conditions of VI-OFF and VI-ON. The comparison between these two conditions will be done via an intention-to-treat approach using a Wilcoxon signed-rank test (non-parametric) due to the small sample size and the unlikelihood of being able to proof normality. For this analysis, data from the baseline testing, the prolonged stimulation period and the long-term follow-up will be used. To compare between the different stimulation algorithms, only descriptive statistics will be applied. The lack of statistical power caused by the small sample size does not allow for a multilevel repeated measures analysis of the data.

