### 2.2. Secondary objectives

*a. To develop a rehabilitation program for VI recipients*

It is expected that patients will benefit from physiotherapeutic rehabilitation during prolonged VI stimulation by improving its functional outcome.

*b. To evaluate the interaction between vestibular and cochlear nerve stimulation*

It is expected that there will be interaction between the stimulation of the vestibular organ and the cochlea. The extent and clinical relevance will be characterized.

*c. To evaluate acute VI performance across several years*

It is expected that the CVI will induce stable VOR responses during acute stimulation over time. The clinical follow-up of the implanted patients will bring new insights for future research.

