#### 8.1.1. Main study parameters/endpoints

The primary objective is assessing the efficacy of the CVI in restoring vestibular function. This will be measured by using a set of vestibular tests, of which DVA will be the main outcome parameter. The tests that will be performed observe two vestibular-related reflex pathways: VOR (gaze stabilization) and VSR (postural balance). The VOR tests consist of the DVA test, the functional head impulse test (fHIT), the 3D video head impulse test (3D HIT) and the torsion swing test. All these tests quantify the VOR at different frequencies and at different levels of functionality. The VSR is observed based on gait and balance tests, looking at the full body response to vestibular stimulation on a functional level. Besides these tests, also the threshold of the perception of movement will be measured using the perception platform.

The main comparison will be made between the measurements done during baseline testing (VI-OFF) and the measurements done during the prolonged stimulation period (VI-ON) (see chapter 2). This will give a

Table 6: Overview of VertiGO! objectives, goals, endpoints and outcome parameters

| Objective |                       |    | Goal                          | Measurement points                                   | Outcome parameters |      |                                                                 |
|-----------|-----------------------|----|-------------------------------|------------------------------------------------------|--------------------|------|-----------------------------------------------------------------|
|           |                       |    |                               |                                                      | Type               | Test |                                                                 |
| Primary   | Prolonged daily stim. | 1a | Overall efficacy              | VI-OFF (baseline) vs VI-ON (stim. weeks)             | Prim.              | Main | DVA                                                             |
|           |                       |    | Adaption to stimulation       | VI-ON (start stim. weeks) vs VI-ON (end stim. weeks) |                    | Aux. | fHIT, 3D HIT, Torsion Swing, Gait analysis, Perception platform |

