|           |                       | 1b | Safety                        | stim. weeks                                          | Sec.               |      | Questionnaires, Interviews                                      |
|           |                       |    |                               |                                                      |                    |      | (S)AE's                                                         |
|           |                       | 1c | Efficacy of 3 stim. types     | VI-ON (week 1) vs VI-ON (week 2) vs VI-ON (week 3)   | Prim.              | Main | DVA                                                             |
|           |                       |    |                               |                                                      |                    | Aux. | fHIT, 3D HIT, Torsion Swing, Gait analysis, Perception platform |
| Secondary | Rehab.                | 2a | Rehab. program                | stim. weeks                                          | Prim.              |      | Gait analysis                                                   |
|           |                       |    |                               |                                                      | Sec.               |      | Questionnaires, Interviews                                      |
|           | CI                    | 2b | Interaction between CI and VI | CI-ON/VI-OFF (baseline) vs CI-ON/VI-ON (stim. weeks) | Prim.              |      | Aided CNC, SPIN, vestibular test                                |
|           |                       |    | CI as part of VCI             | CI-ON (up to 5 years)                                | Sec.               |      | Questionnaires, Interviews                                      |
|           | Long term             | 2c | Acute efficacy                | VI-ON (up to 5 years)                                | Prim.              |      | Subset of vestibular tests                                      |
|           |                       |    |                               |                                                      |                    |      |                                                                 |

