general result on the efficacy of prolonged vestibular stimulation. A further statement of CVI efficacy will be made based on the response to stimulation throughout the different prolonged stimulation weeks. Therefore the VOR tests will be performed several times during the prolonged stimulation weeks. A comparison of these results will yield statements on potential adaptation effects (e.g. habituation to receiving information via the CVI, increase/decrease in response gain and potential increase in VOR alignment). The same set of VOR and VSR tests measured throughout the prolonged stimulation weeks will also serve as parameters for comparing the different stimulation algorithms.

A subset of the vestibular tests will be performed during the annual follow-up visits. These parameters will be used to quantify the stability of acute stimulation and implant functionality over a clinical follow-up period of 5 years.

The functionality of the CI-part of the CVI will be assessed with an aided consonant-nucleus-consonant (CNC) hearing test. This will be done by making the comparison between aided CNC scores using the regular CI processor and aided CNC scores using the CVI processor (the AMP) with both CI and VI part active. During the CI follow-up visits speech in noise (SPIN) tests will be performed as part of the auditory follow-up test set to allow for evaluation of the CI part of the CVI implant and compare this outcome with CI performance of a regular CI implant.

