### ***CI rehabilitation***

CI rehabilitation will be performed as standard in our clinic. This includes a minimum of 11 visits (can be individually extended if necessary) in the time-span of 3 months to establish a fitting and to train the patient with using their CI. The CI rehabilitation period starts around 1 month after implantation. During the first visit a first fitting will be established and the patient will receive their standard CI processor (described in chapter 7), which will be connected to the CVI implant.

Each of the CI rehabilitation visits will take between 1 and 2 hours. During each CI visit, the impedances of all VCI electrodes will be checked. On top of that a short functional test of the VI electrodes will be introduced. This functional VI test will first be piloted in one subject. If the procedure is accepted, the intention is to repeat this functional VI test for each of the upcoming subjects as an extended part (max 60 min.) to three of the regular CI visits. This functional VI test will entail a short, maximum 2 seconds, stimulation of the VI electrode in each of the SSC, starting low in amplitude and increasing in small steps. To generate this stimulation the CI fitting software Maestro will be used. After each stimulation the patient will be asked if they felt something, what they felt and if it is comfortable. As soon as the patient experiences the stimulation as uncomfortable, the test will be stopped. Aside from the subjective feedback, also the eye movements will be captured objectively using video goggles. At no time during this function VI test, or any other moment during CI rehabilitation, the AMP processor will be turned on. The only time patients will actively use the AMP processor is during the VI fitting period and the prolonged stimulation period while they are being supervised in the hospital by the research team.

The final CI fitting visit, 3 months after the start of the CI rehabilitation period will include extra trial related procedures in addition to regular CI procedures. At this point ART measurement will be performed. Also cervical and ocular VEMPs are measured, if they were not absent during inclusion. Alongside this a SPIN hearing test is performed and the patient is asked to fill in questionnaires.

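### Section 10.1 adds long-term follow-up data to the main VI-OFF versus VI-ON comparison, which section 8.1.1 and Table 6 limit to baseline versus the prolonged stimulation period

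*Protocol*

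**What the plan says.** Section 10.1 names the comparison, "The main comparison of the primary outcome parameters will be between the conditions of VI-OFF and VI-ON", assigns it a Wilcoxon signed-rank test on an intention-to-treat basis, and continues: "For this analysis, data from the baseline testing, the prolonged stimulation period and the long-term follow-up will be used".

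Elsewhere the protocol defines the same comparison without follow-up:

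- Section 8.1.1: "The main comparison will be made between the measurements done during baseline testing (VI-OFF) and the measurements done during the prolonged stimulation period (VI-ON").
- Table 6, objective 1a, overall efficacy: "VI-OFF (baseline) vs VI-ON (stim. weeks").
- Section 10.2 analyses the questionnaires in the same way as the primary parameters, but compares baseline with the end of the prolonged stimulation period only.

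Follow-up has its own place. Secondary objective 2c (section 2.2) reads "To evaluate acute VI performance across several years". Table 6 gives its measurement points as "VI-ON (up to 5 years") under the goal of acute efficacy. Section 8.1.1 says of the follow-up tests: "These parameters will be used to quantify the stability of acute stimulation and implant functionality over a clinical follow-up period of 5 years".

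**The concern.** Objective 1a asks whether prolonged daily stimulation works. In section 8.3.6 that means about 8 hours a day on 4 consecutive days, in each of 3 weeks, with the AMP. What patients receive at follow-up is acute stimulation during a check-up visit. If both count as VI-ON in one test, the result answers neither objective 1a nor objective 2c cleanly. A positive result could come partly from acute stimulation, and a weaker acute response could dilute a real effect of prolonged use. A main test that needs follow-up data also cannot be finished until those visits have taken place.

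**Working it through.** **1. The places side by side**

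| Place | VI-OFF | VI-ON |
|---|---|---|
| 8.1.1, main comparison | baseline | prolonged stimulation period |
| Table 6, row 1a | baseline | stimulation weeks |
| 10.2, questionnaires | baseline | end of prolonged stimulation period |
| 10.1, main comparison | baseline | prolonged stimulation period and long-term follow-up |
| Table 6, row 2c (secondary) | not given | up to 5 years |

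The fourth row is the odd one out.

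**2. Is follow-up the same exposure?** Section 8.3.6 (CI rehabilitation) says: "The only time patients will actively use the AMP processor is during the VI fitting period and the prolonged stimulation period". Section 13.1.8 adds that a regular cochlear implant processor drives the implant at all other times. Yet the text on CI follow-up visits says that the vestibular electrodes are stimulated there. By the protocol's own rules, follow-up VI-ON is acute stimulation without the AMP, so it is a different exposure.

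**3. The plan's own figure.** Section 4.4 gives mean logMAR 0.065 (SD 0.061) with the implant active and 0.205 (SD 0.066) inactive, effect size 2.20 and minimal sample size 5.

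- Difference: 0.205 − 0.065 = 0.140.
- SD of differences, with correlation 0.5 (assumed; not stated): √(0.061² + 0.066² − 2 × 0.5 × 0.061 × 0.066) = √0.004051 = 0.0637.
- Effect size: 0.140 / 0.0637 = 2.20, as stated.
- Paired-t power with the sample size multiplied by the Wilcoxon efficiency 3/π, two-sided 0.05: 0.784 at n = 4 and 0.932 at n = 5. So 5 is reproduced under this approximation.

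The calculation takes one difference per patient between implant active and inactive. It has no follow-up term, so removing follow-up from the test leaves it unchanged.

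**4. What mixing could do: an illustration.** Assume one averaged VI-ON value per patient, follow-up with weight w, an acute effect of f × 0.14, and an unchanged SD of differences. The tested effect is then 0.14 × [(1 − w) + w × f]. The DVA scale is used only because it is the one outcome with figures. Power is from the exact signed-rank test at n = 8, with simulated normal differences.

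| f | w | Tested effect | Power, n = 8 |
|---|---|---|---|
| 1 | 0.25 or 0.5 | 0.140 | 0.998 |
| 0.5 | 0.25 | 0.123 | 0.99 |
| 0.5 | 0.5 | 0.105 | 0.96 |
| 0 | 0.25 | 0.105 | 0.96 |
| 0 | 0.5 | 0.070 | 0.69 |

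Conversely, suppose prolonged stimulation has no effect and acute stimulation the full 0.14. The tested effect is 0.14 × w, that is 0.035 (w = 0.25) or 0.070 (w = 0.5). The mixed test rejects in about 23% or 70% of trials, against at most 5% for a test of the stimulation weeks alone. Power suffers little in most of these cases; what the result means suffers more.

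**5. Timing.** Rehabilitation starts about 1 month after implantation, and baseline testing and stimulation fall 6 to 24 months after that start (8.3.6), so at about 7 to 25 months. Follow-up runs to 5 years, or 60 months, after implantation (Summary). If the main test had to wait for all follow-up, the wait per patient would be 60 − 25 = 35 to 60 − 7 = 53 months.

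**The case against.** The strongest reply is that the sentence only lists data sources. Section 8.1 counts all objective outcomes as main parameters, Table 6 labels the objective 2c outcomes as primary-type, and 10.1 covers primary parameters in general. On that view the sentence serves objectives 1a and 2c together, and no single mixed test is meant. This may well be the intent. But the sentence follows directly on the signed-rank comparison and refers back to it, so the wording needs correcting on either view.

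A second reply is that the statistical plan will settle it. Section 10 does call itself an outline, but the definitive plan is due only after the first patient's data are in. Until then the protocol states the choice of periods, and states it two ways.

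A third reply is that the trial is exploratory, takes no structural steps on multiplicity and makes no population-wide claims. That stands, and it lowers the weight of the point.

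A reader might also infer three stronger things that the document does not support:

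- *That the DVA result is contaminated.* Section 8.1.1 says only that a subset of the vestibular tests is done at follow-up, and the overall schedule (Table 1) is not legible in the text at hand. Without the AMP, which converts head motion into pulses, motion-modulated DVA at follow-up is doubtful.
- *That the type I error is inflated because many VI-ON sessions share one baseline.* Nothing says that sessions enter as separate pairs. Section 4.4 treats the patient as the unit, and reducing sessions to one value can be left to the later plan. That problem would in any case lie within the stimulation weeks and has nothing to do with follow-up.
- *That the main result will be delayed by years.* This follows only if the test waits for all follow-up, which the protocol does not say.

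**Conclusion.** Wrong as written. Section 10.1 contradicts 8.1.1 and Table 6 on which periods enter the main comparison, and read literally it mixes acute stimulation without the AMP into the test of prolonged daily stimulation. The contradiction rests on the text alone and needs no calculation.

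Its size cannot be fixed. The figures in the illustration depend on an assumed follow-up weight, an assumed acute effect and an assumed correlation, and they do not show that DVA is affected. The finding concerns the primary parameters as a group. It should be corrected, but it is not critical: the aim is exploratory, and the correct definition already stands in 8.1.1.

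**What to change.** In 10.1, restrict the main comparison to baseline VI-OFF versus VI-ON in the prolonged stimulation period, with the patient as the unit, as in the sample size calculation. Then add a sentence that follow-up vestibular data are analysed separately under objective 2c, for example descriptively. The added sentence is needed: 10.1 is the only place in section 10 that mentions follow-up, 10.2 covers questionnaires and interviews, and 10.3 is marked not applicable. Deleting the phrase alone would leave the objective 2c vestibular data without a stated analysis.

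The cost is two sentences, notified as an amendment under section 12.3. No data are lost, and the sample size and visit schedule stay as they are.

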### Objectives:

#### 1. Primary

- a. To investigate the efficacy of prolonged daily VI stimulation
- b. To investigate the safety of prolonged daily VI stimulation
- c. To investigate the efficacy of three different types of stimulation:

|    | Baseline stimulation | Motion-modulation |
|----|----------------------|-------------------|
| 1) | On                   | Off               |
| 2) | On                   | On                |
| 3) | Reduced              | On                |

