#### Endpoints per objective (see above):

1. Primary objectives
  - a. Primary and secondary outcome measures will be compared between conditions with VI stimulation (VI-ON) versus without stimulation (VI-OFF). The primary and secondary outcome measures will also be used to monitor the effect of prolonged stimulation by comparing outcomes at different time points during the prolonged stimulation period.

[figure not shown]

Figure 1: General overview of the VertiGO! trial schedule

- b. Amount of (S)AE's or other undesired side effects (e.g. psychological burden) derived from secondary outcome measures in relation to prolonged daily VI stimulation.
  - c. Primary and secondary outcome measures will be compared between the different stimulation algorithms used during the different prolonged stimulation periods.
- 2. Secondary objectives
  - a. Tailor made rehabilitation programs
  - b. Primary and secondary outcome measures will be used to investigate the interaction between vestibular stimulation and CI functionality
  - c. A subset of primary and secondary outcomes during long-term clinical follow-up up to 5 years

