## 10. STATISTICAL ANALYSIS

The definitive statistical plan will be constructed after data has been collected for the first patient. Below follows the general outline of the statistical plan.

A single-subject repeated measures design will be used whereby each subject acts as their own control. The outcomes of the different parameters (as described in chapter 8.1) will be bootstrapped and descriptively represented by stating mean and standard deviation, median/interquartile range and minimum/maximum values. Due to the small sample size, normality can most likely not be established, therefore non-parametric statistical tests will be performed. Confidence interval will be set at 95%. Due to the small sample size, the outcomes of this trial are not meant to serve as proof for population-wide claims. The goal of the trial is to assess feasibility of chronic vestibular stimulation with a focus on individual effectiveness (compared to within-subject control) and safety, rather than giving definitive statements on its effectiveness as a treatment for a group of patients.

Since the nature of the trial is exploratory and not confirmatory, the choice is made to include a full set of vestibular tests to assess efficacy of the CVI. The data from this trial will be used to be more rigorous in choosing outcome parameters for a future confirmatory trial with a larger population, in order to reduce multiplicity during that trial. Therefore, during this trial no structural statistical steps are taken to control the impact of multiplicities on the type 1 error. However, care will be taken to avoid combining the results of the different outcome measures into one statement on efficacy. DVA will serve as the main primary outcome for VI efficacy due to it giving objective results on the functional restoration of the VOR response pathway. All other parameters will be viewed as auxiliary.

If missing data are observed, the cause of missingness will be ascertained. When the cause of missingness is suspected to be structural, these cases will be described and excluded from analysis of the affected outcome measure. If data is concluded to be missing at random, the imputation strategy will be decided based on the nature and extend of the missingness. In this process the potential for reduced variance caused by interpolation-based imputation techniques will be taken into account. A final imputation strategy will be decided as part of the definitive statistical plan.

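### Table 6 sets out objective 1c by week although algorithm order is randomised over weeks, and section 10.1 limits this comparison to descriptive statistics where a period-adjusted estimate with an interval is feasible

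*Protocol*

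**What the plan says.** The Summary lists as a primary objective "To investigate the efficacy of three different types of stimulation", and section 2.1c repeats it by stimulation type. The Summary's endpoint for it reads: "Primary and secondary outcome measures will be compared between the different stimulation algorithms used during the different prolonged stimulation periods".

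Table 6 (section 8.1.1) gives the goal of 1c as "Efficacy of 3 stim. types", but in the same row the measurement points are "VI-ON (week 1) vs VI-ON (week 2) vs VI-ON (week 3".

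Section 8.2 randomises the order of the three algorithms using all six possible sequences, each used once or twice, and blinds patients to the algorithm. Section 3.1 explains that patients cannot be blinded to stimulation being on or off.

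Section 10.1 gives the on/off comparison a Wilcoxon signed-rank test. For the algorithms it says "To compare between the different stimulation algorithms, only descriptive statistics will be applied", and it gives the reason: "The lack of statistical power caused by the small sample size does not allow for a multilevel repeated measures analysis of the data".

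Chapter 10 says in general that outcomes will be bootstrapped and "descriptively represented by stating mean and standard deviation, median/interquartile range and minimum/maximum values", and that "Confidence interval will be set at 95" per cent. It ties neither to the difference between algorithms. It calls the trial exploratory and defers the definitive statistical plan until the first patient's data are in.

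**The concern.** There are two linked problems.

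First, because all six sequences are used, every algorithm appears in every week. A comparison of weeks therefore averages over algorithms within each week and mainly picks up practice, repeated rehabilitation and adaptation. An analyst who took the Table 6 cell at its word would not answer objective 1c.

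Second, the comparison between algorithms is the trial's only randomised and patient-blinded one. The on/off comparison sets an earlier baseline day against later stimulation weeks, without randomised order and without blinding. Section 1.4.4 describes the modulated-versus-constant comparison as vital to the case for motion-modulated stimulation. Yet the less protected comparison gets a formal analysis, while the better protected one gets summaries with no adjustment for period and no stated interval for the difference. What is at stake is how precisely, and how free of week-to-week trend, the trial can describe the algorithm differences.

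**Working it through.** **Inputs.** From section 4.4: DVA means of 0.065 (SD 0.061) with the implant active and 0.205 (SD 0.066) inactive, effect size 2.20, minimal sample size 5, planned sample 8 to 13. From section 8.2: the urn rule. Not given and therefore assumed: the within-patient correlation r, any weekly trend, and that the on/off SDs carry over to differences between algorithms.

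**The plan's own figure.** SD of a within-patient difference = sqrt(0.061² + 0.066² − 2r × 0.061 × 0.066). At r = 0.5 this is sqrt(0.003721 + 0.004356 − 0.004026) = 0.0636, and 0.140 / 0.0636 = 2.20. The stated effect size therefore corresponds to r = 0.5. With the usual asymptotic-efficiency approximation for the Wilcoxon test under a normal parent, two-sided power is 0.784 with 4 patients and 0.932 with 5, so the stated 5 is reproduced. The protocol states no figure for the algorithm comparison.

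**Is the adjusted model estimable with 8 patients?** There are 8 × 3 = 24 patient-weeks. Residual degrees of freedom = 24 − 1 − 7 (patients) − 2 (periods) − 2 (algorithms) = 12.

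**Cost of adjusting for period.** With 8 patients the urn holds six sequences plus two different extra ones, so 15 compositions are possible. Without period, the variance of a pairwise difference is 2/8 = 0.25 times the residual variance. With period it lies between 0.25 and 0.2625 over the 15 urns. Largest ratio: 0.2625 / 0.25 = 1.05, that is, 5%. It is 3.1% with 10 patients and 0% with 6 or 12.

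**Width of the interval.** Half-width = t(0.975; 12) × (SD of difference / √2) × sqrt(0.2625), with t = 2.179, 8 patients and the least favourable urn:

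| Assumed r | SD of difference | 95% half-width (logMAR) |
|---|---|---|
| 0 | 0.0899 | 0.071 |
| 0.5 | 0.0636 | 0.050 |
| 0.8 | 0.0404 | 0.032 |

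Without period, the half-width at r = 0.5 is 0.048. With 12 patients and r = 0.5 the adjusted half-width is 0.038.

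**Size of the bias removed.** The six basic sequences give each algorithm a mean period of 12/6 = 2. Two extra sequences that both begin with the same algorithm give that algorithm (12 + 1 + 1)/8 = 1.75 and the other two (12 + 2 + 3)/8 = 2.125, a gap of 0.375 week. Over the 15 urns the gap is 0 in 3, 0.25 in 6 and 0.375 in 6, so 12 of 15 are unbalanced.

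For an assumed linear trend of 0.02 to 0.07 logMAR per week, the distortion of a raw difference is at most 0.375 × 0.02 = 0.0075 to 0.375 × 0.07 = 0.026. If 2 of 8 patients are lost at random (section 8.5 excludes replacement after implantation), about 84% of outcomes are unbalanced, with a mean gap of 0.43 week and a maximum of 1.0 week. The worst distortion is then 0.02 to 0.07 logMAR.

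**The case against.** The strongest defence is that the protocol is openly exploratory, disclaims population-wide conclusions and makes a declared choice of descriptive statistics for a contrast it expects to be underpowered. Much of this stands.

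- A reader might infer that objective 1c itself is defined by week. It is not. The Summary, sections 2.1 and 8.1.1, section 10.1 and the goal in the same Table 6 row all define it by algorithm. Table 4 labels each week as a randomised algorithm, so the cell may be shorthand for the stimulation block.
- A reader might infer that no interval is planned at all. Chapter 10 foresees bootstrapping and a 95% level in general; what is missing is the link to the algorithm differences.
- A reader might infer that section 4.4 shows ample power for the algorithms too. It does not. Its 0.14 logMAR is an on/off effect, and section 1.4.4 reports benefit from unmodulated stimulation as well, so differences between active conditions may be smaller. At r = 0.5 with 8 patients, simulated power of an exact signed-rank test is 0.998 for 0.14, but 0.69 for 0.07 and 0.42 for 0.05. The caution about testing is justified.
- A reader might infer that raw comparisons would be badly biased. With complete data the imbalance is small, and the documents give no weekly trend.

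DVA is also measured on four days each week, so a fully multilevel model of days within weeks within patients is more demanding than the additive model considered here. The defence does not show why low power should rule out an adjusted estimate with an interval. Nor can the point simply be left to the later plan, because section 10.1 fixes the restriction in words that the plan would inherit.

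**Conclusion.** The point holds as an internal inconsistency in one table cell and as a cheap improvement to section 10.1. It does not undermine the trial, and the descriptive choice is a disclosed one. The adjusted comparison is estimable at the minimum planned size, costs at most 5% in variance, and gives a 95% half-width between 0.032 and 0.071 logMAR as the assumed correlation falls from 0.8 to 0. These widths rest on the on/off SDs applying to differences between algorithms, on additive patient, period and algorithm effects, and on the protocol's own expectation of minimal carry-over. The gain in bias is modest with complete data and larger after dropout. The main gain is an algorithm estimate with its uncertainty stated.

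**What to change.** In Table 6, replace the measurement points for 1c with baseline plus modulation versus reduced baseline plus modulation versus unmodulated baseline, each in its randomised week.

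In section 10.1, state that within-patient DVA differences between algorithms, led by modulated against unmodulated, will be estimated with adjustment for patient and period. They should carry 95% intervals, by bootstrap or from the model in line with chapter 10, and be labelled exploratory with no confirmatory test. The definitive plan should fix which summary of the four daily DVA measurements represents each week. Reword the last sentence of 10.1 to say that power is too low for confirmatory testing between algorithms.

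The cost is a table cell, a few sentences and one extra model on data already planned. The downsides are a mild additivity assumption and intervals that will be wide relative to the differences if those are small.
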